**Figure 1 figure1:**
[figure not shown]
Study design.

### Participants and Selection Criteria

Study participants will be recruited from a pool of individuals who are insured by the TK—a statutory health insurance organization based in Hamburg. To be included in the study, participants must be eligible for PERS reimbursement, have a “care level” (Pflegegrad) as defined under the German health care system of at least 1 and at most 4, and be of at least 18 years of age.

Exclusion criteria for the study are severe cognitive impairments, severe hearing impairments, severe motor impairments, mental disorders, or other medical conditions that prohibit participation due to the inability to provide consent or to communicate with the case manager over the phone. Participants who are expected to be outside the home for a significant amount of time (due to planned hospital admission, for example) of the intervention period will be excluded. This applies to any single period of over 3 weeks or a cumulative period of over 2 months.

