## Methods

### Study Design and Overview

The Sicher Zuhause study is a prospective interventional study with an intervention arm of 500 participants, which is compared to a matched population derived from historical PERS subscribers. The study tracks the health care utilization and expenditure of the participants over 8 months. During this period, the participants in the intervention arm may receive calls from one of the case managers in the study with the offer to discuss the participant’s health status and care needs. Based on this discussion, the case manager may recommend one or more interventions.

The matched population serving as a control group does not actively take part in the study and is instead derived from the historical records of PERS subscribers. This population will be matched with the intervention arm to be as similar as possible compared to the intervention group using propensity score matching. An overview of the study design is shown in Figure 1.

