#### Data Analysis

The analysis of the primary outcome, the number of hospitalizations, will be based on a comparison of reimbursement records between the intervention arm and a matched population acting as a control group. Propensity score matching will be used to obtain a comparable control group [14,15] using a large pool of population characteristics (over 100 variables), which include the age at enrollment, gender, geographic location, care level, and presence or absence of common medical conditions. The intervention arm of 500 participants will be compared to an equal-sized matched control group of 500, determined by propensity score matching out of an initial pool of approximately 5000 candidates. Differences between groups will be analyzed through statistical testing, using the binomial rate test for the number of admissions and the t-test for differences in costs.

Analysis of the qualitative data provided by questionnaires will focus on evaluating the participants’ satisfaction with the Sicher Zuhause program overall, and with the individual components such as the case manager interactions and the offered interventions. This will be done through descriptive statistics such as the mean and standard deviations of the satisfaction and helpfulness measured on Likert scales.

The qualitative data will be used to provide insights into to outcomes of the primary objectives and may assist in the improvement of the CareSage predictive model.

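### The expected-absence exclusion screens long planned admissions out of the intervention arm but cannot be mirrored in historical controls, which biases the comparison toward benefit by an unknown amount

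*Protocol article*

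**What the plan says.** Participants and Selection Criteria, in the protocol article, lists two kinds of exclusion. The first covers impairments and conditions "that prohibit participation due to the inability to provide consent or to communicate with the case manager over the phone". The second covers expected absence: "Participants who are expected to be outside the home for a significant amount of time (due to planned hospital admission, for example"). The threshold follows: "This applies to any single period of over 3 weeks or a cumulative period of over 2 months".

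Study Design and Overview describes the comparator, which comes from PERS subscribers: "The matched population serving as a control group does not actively take part in the study and is instead derived from the historical records". Data Analysis selects these controls by propensity score matching on more than 100 variables, "which include the age at enrollment, gender, geographic location, care level, and presence or absence of common medical conditions". It then states: "The intervention arm of 500 participants will be compared to an equal-sized matched control group of 500", drawn from a pool of about 5000.

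The primary outcome in Objectives is the number of hospitalizations over 8 months, with no exception for planned ones. Hospital days and hospital-related costs are among the secondary outcomes. The Discussion concedes that a retrospective control group may bring selection bias, which matching addresses only in part.

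**The concern.** The only example the absence rule gives, a planned hospital admission, is itself an outcome event. A person facing a long planned stay is turned away from the intervention arm before follow-up begins. The same person in the historical pool can be matched as a control, and the stay then counts in the primary outcome and in the secondary outcomes of hospital days and costs.

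The difference arises before any risk score or case-manager call, and it favors the intervention. Hospital days and costs are the more exposed outcomes, because one stay of over 3 weeks adds a single event to the count but many days to the total.

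**Working it through.** **Step 1. Can the rule be carried over to controls?**

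- *Nature of the criterion.* It is an expectation held at enrollment. Controls are not enrolled, so nobody elicits it from them.
- *Data sources.* Data Collection names reimbursement records, response center data, case-manager notes and an end-of-study questionnaire. None is described as recording an expected absence.
- *Matching variables.* Those named are age, gender, location, care level and common medical conditions. None is a planned admission or an expected absence.
- *Using actual absences instead.* This would remove controls because of hospital stays during follow-up, which is selection on the outcome.

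On the article's own description, the asymmetry therefore remains after matching.

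**Step 2. The article's own benchmark.** Sample Size Calculation uses 23% versus 32%, 80% power and alpha 0.05. Two-sided, with pooled variance and no continuity correction:

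n = [1.960 × √(2 × 0.275 × 0.725) + 0.842 × √(0.23 × 0.77 + 0.32 × 0.68)]² / 0.09² = 385.2, rounded up to 386 per group.

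This reproduces the stated 386. Allowing for 15% loss, 386 / 0.85 = 454.1 against the stated 454. The planned effect of 9 points is the yardstick below.

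**Step 3. Size of the bias under stated assumptions.** Let f be the share of matched controls who would have been excluded for a long planned admission, and q their probability of hospitalization. The article gives neither. Assume no treatment effect and a base risk of 0.32. Then:

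- control risk = (1 − f) × 0.32 + f × q
- spurious difference D = f × (q − 0.32)

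With q = 1 (the planned admission always takes place), D = 0.68 × f. The chance of a falsely significant benefit is Φ[(D − 1.96 × SE₀) / SE₁] at 500 per group, where SE₀ uses the pooled and SE₁ the separate variances. The nominal value is 2.5%.

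| f (of 500 controls) | D, points | Share of 9 points | Chance of false benefit |
|---|---|---|---|
| 1% (5) | 0.7 | 8% | 4.2% |
| 2% (10) | 1.4 | 15% | 6.7% |
| 5% (25) | 3.4 | 38% | 20.5% |
| 10% (50) | 6.8 | 76% | 61.4% |

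Worked row, f = 5%: the control risk is 0.95 × 0.32 + 0.05 × 1 = 0.354, so D = 0.034. SE₀ = √(2 × 0.337 × 0.663 / 500) = 0.0299, and SE₁ is also 0.0299. Then (0.034 − 0.0586) / 0.0299 = −0.82, and Φ = 0.205.

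With q = 0.6, D runs from 0.3 points (f = 1%) to 2.8 points (f = 10%), and the chance of false benefit from 3.1% to 15.3%.

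The 32% is a 180-day proportion from the cited study. It is used here for an 8-month count outcome because the article gives no other base risk.

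**The case against.** Several points against the concern are fair.

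- **All exclusions.** A reader might infer that every exclusion acts on the intervention arm alone and removes high users from it. The article does not support that. It does not say how the pool of 5000 was filtered, and an article may leave such filtering to the full protocol. The impairment criteria ("severe cognitive impairments, severe hearing impairments, severe motor impairments, mental disorders") apply only where they prevent consent or phone contact. They could be filtered in claims or partly balanced through care level and the other matching variables. Nor does the article show that people excluded for impairment are hospitalized more often, so no direction of bias follows for them.
- **A large bias.** A reader might suppose that 10-20% of controls would be excludable, with 1.5 to 2 times the hospitalization rate of the rest. The control rate would then be inflated by a factor of 0.90 + 0.10 × 1.5 = 1.05 up to 0.80 + 0.20 × 2 = 1.20, a spurious rate ratio of 0.95 to 0.83. Neither input is in the article, and the arithmetic describes an unmatched pool, whereas matching could lower the share.
- **A narrow rule.** It covers only long absences, not all of them hospital stays. Shorter planned admissions remain eligible in both groups.
- **Disclosure.** Selection bias is already acknowledged in general terms.

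These points limit the scope and leave the size open, but they do not remove the asymmetry for long planned admissions. Filtering on diagnoses cannot supply an expectation that was never recorded. The general caveat mentions neither this rule, nor the direction of its effect, nor that an outcome event is screened out of one arm. The list of matching variables is not exhaustive, so a proxy may exist, but the article names none.

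**Conclusion.** The concern holds for the expected-absence rule and planned admissions. As described, the design keeps long planned admissions out of the intervention arm and allows them among controls, and the resulting bias favors the intervention.

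The size is unknown. Under the assumptions in the working, it is small if 1-2% of matched controls are affected and material against the planned 9 points at 5-10%. The calculation assumes a base risk of 32%, no treatment effect, and a planned admission that always takes place; a lower probability shrinks the bias in proportion to q − 0.32.

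The finding does not extend to the impairment exclusions. It also does not justify replacing the primary outcome with unplanned admissions, since the rule reaches only absences over 3 weeks or over 2 months in total.

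**What to change.** 1. Before matching, apply the eligibility criteria of Participants and Selection Criteria that records can identify to the control pool. Do this at each control's index date, using only data from before that date.
2. Keep the number of hospitalizations as the primary outcome. Prespecify a sensitivity analysis of hospitalizations, hospital days and costs that leaves out planned (elective) admissions in both groups, as far as the reimbursement records identify them.
3. Name in the limitations that expected absence cannot be mirrored in controls, and that the bias runs toward benefit.

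The cost is a control pool somewhat smaller than 5000 and reliance on imperfect code-based proxies. The article says only that the records hold type of care and cost, so whether they separate elective from other admissions must be checked first. Recruitment and the intervention are unaffected.

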### Enrollment

Potential study participants will be recruited through one of several ways:

New PERS customers or customers of the nursing service of ServiceCall or the DRK who are insured at the TK will be asked if they are interested in learning about the study.Potential participants may be made aware of the study through articles published by the TK (for example, in their member magazine).Potential participants may be identified from among existing TK customers. These potential participants may be contacted directly by the TK by phone or mail.

Identified individuals will be sent an information letter and informed consent. Individuals will be enrolled in the study after returning the signed informed consent letter.

### Study Sites

The participants will use the PERS service in their own homes. During the study, the participants will make use of one of two response centers operated by ServiceCall (Kassel, Germany) and DRK (Düsseldorf, Germany).

### Risk Score Calculation

During the study, the participants’ risk will be assessed by a predictive model of hospital transport in the next 30 days. This predictive risk model was developed on a retrospective data set of more than 8000 deceased German PERS subscribers using a methodology similar as described in [7], which is used by the Philips CareSage predictive analytics engine in the United States. The predictive model achieved an area under the receiver operator characteristic curve of 0.75.

The predictive model calculated the participants’ risk based on a combination of medical alert pattern data collected by the call centers, as well as demographic information and self-reported medical conditions. The provided risk score is relative to the average risk of the population used to develop the model (eg, a risk of 2 indicated an estimated risk two times higher than the average). The distribution of the risk scores will be monitored during the study in case there are major differences between the study population and the population used to develop the model.

### Intervention

Throughout the study, risk scores will be calculated daily and provided to a case manager. While risks are predicted for 30 days, daily calculations of the risk score allow for new information to be taken into account as soon as possible. Based on the height and trend of the risk scores, the history of response center interactions and demographic data, the case manager decides which participants to contact to further inquire about their health status and care needs (Figure 2).

**Figure 2 figure2:**
[figure not shown]
Intervention protocol.

When a case manager contacts a participant, they will first evaluate the participant’s health status through a triage protocol. Based on this conversation, the case manager may conclude to offer one or more interventions. As part of this study, the case manager may recommend:

No further action is needed at this time.To plan a general practitioner visit.To contact emergency medical services.To enroll in one of the TK’s existing health and care offers. These can, for example, include training programs on nutrition, a fall prevention course, or cardiovascular training.To schedule a care consultation.

Interventions by the TK are offered free of charge. If one or more interventions are recommended, the case manager will schedule a follow-up call with the participant after 14 days. During the follow-up call, the case manager will inquire if the participant followed the suggested actions, and if so, what was the outcome (eg, referral to a specialist or dietary recommendations).

At the start of the study, participants will also receive a welcome call from the case manager to obtain a baseline measure of the participant’s health status and already plan interventions if necessary. The participant may ask any questions that remain regarding the study.

### Data Collection

The main source of data for the analysis of health-related outcomes will be the reimbursement records collected by the TK. These contain the type of care and the associated costs of care received by the participants during the intervention period. The expected time for these records to become available to the TK is approximately 1 month for hospital and PERS-related costs, and up to 9 months for ambulatory and specialist costs. At the end of the study period, participants will be asked to complete a questionnaire on health care utilization during the intervention period.

Response center data, including records of interactions with the personal response agents, demographics, and reported medical conditions, will also be collected during the intervention period for risk score calculation and the evaluation of the study. The case managers will also document the recommended interventions and actions taken by the participant during the follow-up call after an initial recommendation.

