## Discussion

This protocol describes a study that aims to determine if the combination of risk scores determined through predictive modeling and interventions offered by a case manager can result in a reduction of hospital admissions and health care costs in a German PERS subscriber population. The rapidly aging population with multiple comorbidities presents numerous challenges to effective care management, and therefore, alternatives to hospital and institutional care are needed to optimize health care costs and improve patient outcomes [17]. In the future, the results of this study can lead to better health outcomes for the population described.

This study has a few limitations. First, it does not include a randomized design, and the use of a retrospective control group may lead to selection bias. In the study, this concern is partially addressed by the use of propensity score matching. Second, the effect of the risk prediction and the interventions cannot be easily separated. As such, the study aims to evaluate the combination of the two, where the predictive model helps to identify the right subset of participants to whom interventions should be offered. Further, analysis of the qualitative data can help to provide insights into the performance of the predictive model and the effectiveness of the interventions. Another option would be to include additional study arms; however, due to the expected recruitment rate, this is likely not feasible.

A third limitation is that it might be difficult to capture data on health care utilization that may be initiated outside of the PERS service. Capturing emergency department visits and hospitalizations is important because the study population is a high health care utilization group that is at risk for emergency transport, and patients are typically taken to the nearest medical center for emergency care services. However, self-reported data from patients may help mitigate some of these challenges.

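### Matched groups are compared with unadjusted tests, and prior hospital use and cost are not among the named matching variables, so a difference that survives matching would count as programme effect

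*Protocol article*

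**What the plan says.** All references are to the protocol article.

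- **Source of outcomes (Data Collection).** Health outcomes come from TK reimbursement records, which hold "the type of care and the associated costs of care received by the participants during the intervention period". The follow-up is 8 months (Study Design and Overview).
- **Confounding control (Data Analysis).** "Propensity score matching will be used to obtain a comparable control group": 500 controls are chosen from about 5000 candidates on more than 100 variables, "which include the age at enrollment, gender, geographic location, care level, and presence or absence of common medical conditions".
- **Outcome tests (Data Analysis).** Groups are compared "using the binomial rate test for the number of admissions and the t-test for differences in costs". No covariate, baseline value, change from baseline or pairing is named.
- **Who is compared (Enrollment; Study Design and Overview).** Participants enter by returning signed consent. Controls come from past subscriber records and do not take part.
- **Stated limitation (Discussion).** The authors accept that "the use of a retrospective control group may lead to selection bias" and say that propensity matching answers this only in part.

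**The concern.** People who agree to a programme of telephone case management may differ from those who were never asked, in ways that age, care level and diagnoses do not fully capture. The eligibility rules add to this. Participants are screened out if they expect long absences from home, with a planned hospital admission given as an example, or if they cannot consent or communicate by phone. The article does not say that these screens are applied to control candidates, and an expected absence would be hard to reconstruct from past records.

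Prior hospitalizations and prior cost are the pre-enrolment counterparts of the outcomes themselves. They are the most direct check on whether the groups were comparable before the programme began. The article names neither as a matching variable and describes no use of them in the outcome analysis. In a non-randomized study, the conclusion rests on comparability. Whatever imbalance remains after matching goes into the estimate, and the stated tests would neither show it nor correct it.

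**Working it through.** **Inputs from the article (Sample Size Calculation; Data Analysis).** 23% versus 32%, alpha 0.05, power 80%, loss to follow-up 15%, 500 per group. The article gives no pre-enrolment gap and no correlation between prior and current use, so those below are assumptions.

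**1. The plan's own figure.** Two-sided test of two proportions, pooled under the null, mean proportion 0.275:

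n = [1.96·√(2·0.275·0.725) + 0.842·√(0.32·0.68 + 0.23·0.77)]² / 0.09² = 385.2, which rounds up to 386 per group, as stated.

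386/0.85 = 454.1, which agrees with the stated 454 within rounding. The sample size is not in question here. At 500 per group with 15% loss, 425 remain.

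**2. Bias on the ratio scale.** Planned ratio: 23/32 = 0.72. Suppose matched participants would have had a 10% lower rate without any programme (32% becomes 28.8%). A programme with no effect then shows a ratio of 0.90, and

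ln(0.90)/ln(23/32) = 0.32,

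about a third of the planned effect.

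**3. False-positive rate.** Assume no programme effect, controls at 32%, and a gap g that survives matching, so participants are at 32% − g. With SE₀ the pooled and SE₁ the unpooled standard error, the two-sided rejection rate is

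Φ[(g − 1.96·SE₀)/SE₁] + Φ[(−g − 1.96·SE₀)/SE₁].

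For g = 0.03 and 500 per group, SE₀ = 0.02912 and SE₁ = 0.02910, which gives 0.1761 + 0.0014 = 17.8%.

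| Surviving gap (points) | 500 per group | 425 per group |
|---|---|---|
| 0 | 5.0% | 5.0% |
| 1 | 6.3% | 6.1% |
| 2 | 10.5% | 9.7% |
| 3 | 17.8% | 15.8% |
| 4.5 | 34.3% | 30.0% |

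This uses the planning proportions over 180 days as a stand-in. The primary outcome is a number of hospitalizations over 8 months, so the table shows the order of magnitude only.

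**4. From a gap in prior use to a gap in outcome.** A gap of D standard deviations in prior use carries forward as about r·D, where r is the correlation between prior and current use. The rejection rate at 500 per group is Φ(rD/√(2/500) − 1.96) + Φ(−rD/√(2/500) − 1.96).

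| D | r = 0.3 | r = 0.5 |
|---|---|---|
| 0.1 SD | 7.6% | 12.4% |
| 0.2 SD | 15.8% | 35.3% |

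**5. Precision.** In a linear model, adjusting for the prior value leaves a share 1 − r² of the variance. With r = 0.3 this is 0.91 and with r = 0.5 it is 0.75, so adjustment removes 9% to 25% of the cost variance. Adjustment need not cost power.

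**The case against.** The strongest reply is that confounding control has been placed in the design stage. Matching on more than 100 variables from a pool ten times the size needed, followed by a simple two-group comparison, is a recognised approach. The list of variables is open, and a journal article commonly leaves the full list to other documents. The limitation is also disclosed.

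Most of this stands, and it rules out three stronger readings that a reader might infer:

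- *That every pre-existing difference becomes programme effect.* It does not. Only what survives matching passes through, and a gap in prior use carries into the outcome only in proportion to its correlation with it.
- *That the plan leaves prior use out of the matching, or restricts all claims data to the follow-up.* The article does not say so. The sentence in Data Collection describes outcome records, which naturally come from the intervention period; it is silent on the source of matching variables.
- *That TK is stated to hold prior claims for both groups.* This is an inference, though a strong one: participants are TK insured, outcomes come from TK records, and Data Analysis compares reimbursement records between the two groups.

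What the reply does not answer is the choice of outcome test, which the article does fix. Even if prior use is in the score, matching gives approximate balance, and the authors themselves call it partial. No further step is described for the remainder.

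**Conclusion.** The point holds in a limited form. The stated outcome tests make no baseline adjustment, and prior hospital use and cost are not named for matching, so a difference that survives matching would be attributed to the programme. An assumed 10% lower residual rate would alone produce about a third of the planned log effect. An assumed residual gap of 2 to 4.5 points would put the false-positive rate at roughly 10% to 34% instead of 5%. These sizes rest on assumed gaps, and the article gives no evidence on how large the real one will be. If prior use is already in the score and well balanced, the bias from this source is small, and the case for adjustment is then mainly one of precision. The change should be made because it reduces bias, is likely to improve precision and costs little; the article contains no arithmetical error on this point.

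**What to change.** 1. Where TK claims allow, extract a fixed pre-index window, for example 12 months, for participants and control candidates alike. State how the index date is set for controls.
2. Ensure that prior hospitalizations, hospital days and costs from that window are in the propensity score, and report balance on them after matching.
3. Replace the unadjusted tests with outcome models adjusted for these values: a count model for hospitalizations and a regression for costs.
4. Optionally, add a difference-in-differences estimate as a sensitivity analysis.

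The cost is one further claims extraction and a check that consent and data-protection terms cover the earlier period. Recently insured persons will have incomplete history, so a rule for handling them should be set in advance. If prior use is already in the score, one sentence saying so settles the matching part, and steps 2 (balance) and 3 remain.
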